### Data collection procedure

Once participants are contacted, informed and agree to participate in the study, data will be collected for subsequent statistical analysis. Some information will be recorded using paper and pencil. The documents will be applied by themselves, and in this instance one of the researchers ([name]) will monitor the participants to answer any questions they may have. Others will be recorded through the audiobook application.

Data security and confidentiality will be safeguarded throughout the complete information collection process.

Sociodemographic data will be individually asked to each older adult during the baseline assessment. Specifically, we will obtain information about age, gender, and educational level.

Secondly, we will apply the DIGCOMP questionnaire to assess the older adults’ digital competence. Furthermore, part A of the well-being questionnaire will be applied obtaining the current Hedonic, Eudaimonic, and Social well-being perception before using the application.

The duration of the intervention will be 4 weeks. During this period, the audiobook application will collect information automatically every time the audiobook application is used. Information to be collected include the poems listened, date, hour and reproduction time that the participants listened to each poem. This information will be stored in a remote database.

In the exit assessment, the application of part B of the well-being questionnaire will be done, obtaining the perception of the older adults’ Hedonic, Eudaimonic and Social well-being after the intervention. In addition, the usability questionnaire (SUS) will be applied to the older adults to assess the audiobook application’s usability.

### Statistical analysis

For data analysis, a single database will be created with the results obtained from the application of the questionnaires, the older adults’ sociodemographic characterization, and the information collected automatically by the application.

Subsequently, descriptive statistics will be used for univariate and bivariate frequency analysis which will consider measures of central tendency (mean and standard deviation) to describe the characteristics of the sample and the questionnaire results.

Then, the study hypothesis will be carried out using a multivariate linear regression in order to characterize the well-being variable at the end of the intervention, controlled by the initial well-being, and by sociodemographic variables, usability and frequency of use.

We will explore if the covariates play a role of confounding effects and/or modifiers in the relationship between the initial and the final well-being score. The specific model is assumed to be a Generalized Linear Model, for normal distribution and identity link. Data processing and analysis will be performed using the IBM SPSS Statistics for Windows, Version 28.0 (IBM Corp. Released 2021, Armonk, NY, USA).

Data analysis will be performed under an intention-to-treat (ITT) approach by a researcher blinded to the study group. The multiple imputation technique [36] will be applied using the predictive mean matching method to handle missing data and ensure the inclusion of all participants in the analysis.

The proposed statistical model is summarized as follows:
$$\begin{array}{c} \begin{array}{c} B_{final}=a_{0}+b\left(B_{initial}\right)+b\left(frec\right)+b\left(usability\right)+b\left(gender\right)+b\left(other\;dem\right) \end{array} \end{array}$$
where

*B*_*final*_ : Final well-being score.*a*_0_ : Intercept.*b*(*B*_*initial*_) : Slope associated with initial well-being.*b*(*frec*) : Slope associated with the application’s frequency of use.*b*(*usability*) : Slope associated with the application’s evaluated usability.*b*(*gender*) : Slope associated with the participants’ gender.*b*(*other*
*dem*) : Slopes associated with other confounding demographic variables or relevant modifying effects.

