### Objective, research question and hypothesis

The goal of this 4-week quasi-experimental study is to assess the impact of an audiobook mobile application on the well-being perception of older adults belonging to a Community Rehabilitation Center (CRC) at Concepcion, Chile, and to evaluate the usability of the mobile application designed for this population.

Our research question is the following: Does listening to audio poems using a mobile application improve the perception of well-being of the older adults who go to the CRC at Concepción?

Finally, our hypothesis is that using a mobile application that allows listening to poems produces a positive change in older adults’ perception of well-being.

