### Design

A quasi-experimental study will be conducted during the second quarter of 2024 to assess the improvement in the well-being perception of older adults and the usability of an audiobook mobile application. This design is based on the desire to reduce ethical considerations (ethical problems of randomizing patients), avoid data contamination, and offer a more cost-effective and feasible approach for implementing this research [25–27]. In this study, participants will be compared with themselves at the beginning and at the end of the intervention, that is, a pretest/posttest with a single group.

Fig 4 shows the study protocol’s flow diagram. The first stage at the top corresponds to recruiting community-dwelling older adults, to be done at a community center (recruitment will begin at the end of April 2024 and be completed at the end of May 2024) by two of the researchers ([name], [name]). With the older adults who agree to participate in the study, we ([name], [name]) will do the second stage (screening), which consists of determining who can participate in the study by applying the inclusion and exclusion criteria (third stage). Before starting the intervention, participating older adults must accept and sign a written consent (fourth stage). Some of them may refuse to participate in the study and thus be excluded from it (fifth stage). Then, a baseline (sixth stage) will be established by applying standardized and validated tests to the participating older adults, who will then have an induction session, in which the three researchers will participate ([name], [name], [name]), to install the application on their smartphones, learn how to use the application and get answers to any questions they might have (seventh stage). In the intervention (eighth stage), the participants will use the application for four weeks (during June 2024), with a follow-up at 2 weeks (ninth stage) to be performed by two of the researchers ([name], [name]). After these four weeks of application use, the older adults will be evaluated through standardized tests (tenth stage). Finally, the data obtained from the questionnaires and from using the audiobook itself will be analyzed (eleventh stage).

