### Recruitment

The participants will be recruited from the Community Rehabilitation Center at Concepción, Chile. We estimated our sample size considering a pre-post difference of 1,24 points on the mental health outcome [28] and a potential standard deviation of 3,4. Thus, we planned for a sample size of 60 individuals [29] with a continuous response variable measured pre-post intervention to be able to reject the null hypothesis that the response difference is zero with power 0,8 and an error probability of 0,05. The sampling technique will be non-probabilistic and will be used for the convenience of the study.

Recruitment flyers will be posted on the walls of the CRC to make an open call to all people over 60 years of age being treated at that place. Furthermore, group meetings scheduled by the researchers ([name], [name]) will be held at the CRC offices to invite older adults to participate in the research. Older adults interested in the study will register by giving their name and telephone number, and will be contacted later by the researchers ([name], [name]).

Older adults interested in participating in the study will be contacted by telephone. Then, the study, the objectives of the research and the strategy to be used in the study will be explained to them in a concise and precise way. Furthermore, they will be questioned to find out if they meet the inclusion criteria for the study. Inclusion and exclusion criteria are shown in Table 1.

**Table 1 pone.0312463.t001:** Inclusion and exclusion criteria.

Inclusion Criteria	Exclusion Criteria
Person aged 60 and over who belongs to the CRC at Concepción. Speak and read Spanish. Enabled and capable of approving the informed consent. Provide signed informed consent. Older adults who have a smartphone where they can run the audiobook mobile application. Older adults who are not participating in other emotional, social and/or motor training programs.	Significant psychiatric or medical illness (depressive disorder, delirium, intellectual disability, etc). Older adults classified with dependency criteria. Illiterate people. Presence of a severe sensory deficit, either in visual or hearing difficulties. Presence of neurodegenerative diseases (dementia, Alzheimer’s disease, Parkinson’s disease, multiple sclerosis, etc.).

If the older adults refuse to participate, they will be thanked and told there is no harm to them. Otherwise, they will be invited to a meeting at the CRC, on a schedule to be agreed.

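### No coefficient in the planned regression equals the mean pre-post change, which is what the hypothesis concerns and what the 60 participants are powered to detect

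*Protocol article*

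**What the plan says.** Four places in the protocol article bear on this point.

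- **Objective, research question and hypothesis:** "our hypothesis is that using a mobile application that allows listening to poems produces a positive change in older adults’ perception of well-being".
- **Design:** participants are compared with themselves, in "a pretest/posttest with a single group".
- **Recruitment:** the sample size was set "considering a pre-post difference of 1,24 points on the mental health outcome" with "a potential standard deviation of 3,4". Sixty participants are planned "to be able to reject the null hypothesis that the response difference is zero with power 0,8 and an error probability of 0,05".
- **Statistical analysis:** the hypothesis is given to a "multivariate linear regression in order to characterize the well-being variable at the end of the intervention, controlled by the initial well-being". The equation is written out: final score equals an intercept plus terms for initial score, frequency of use, usability, gender and other demographics. The section also says that covariates will be explored as "confounding effects and/or modifiers in the relationship between the initial and the final well-being score". The only other planned analysis of the questionnaires is descriptive (means and standard deviations).

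Under Outcome measures, Part A of the well-being questionnaire (before) has 6 questions and Part B (after) has 12, all scored 1 to 5.

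**The concern.** The hypothesis and the sample size both concern the size of a mean change over four weeks. The model given to that hypothesis describes something else: which participants end with higher scores than others, given where they started. It has no group term, because there is one group, and it has no time term or change score.

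Followed as written, the hypothesis-testing analysis gives no designated estimate, confidence interval or p-value for the change that the study was sized to detect. The stated power of 0.8 belongs to a test that the analysis section does not name.

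The exploratory aim has the same difficulty. In a single-group study the association between initial and final score shows how well scores track over time. It is not an intervention effect that covariates could confound or modify.

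**Working it through.** **1. Reproduce the sample size.** Inputs from Recruitment: difference 1.24, SD 3.4, power 0.80, alpha 0.05. The article does not state the sidedness or whether 3.4 is the SD of the difference. Taking two-sided alpha and the SD of the difference:

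n = (SD × (z₀.₉₇₅ + z₀.₈₀) / difference)² = (3.4 × 2.8016 / 1.24)² = 59.01, rounded up to 60.

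The exact paired t-test has power 0.794 at n = 60 and reaches 0.80 at n = 61, which is a trivial gap. Other readings do not give 60:

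| Reading | n |
|---|---|
| One-sided alpha 0.05 | 47 |
| Two independent means | 119 per arm |
| 3.4 as SD of a single score, pre-post correlation 0.3 | 83 |
| Same, correlation 0.7 | 36 |

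At correlation 0.5 the single-score reading also gives 60, because the SD of the difference is then again 3.4. Either way, the figure belongs to a paired test of mean change.

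**2. What the planned coefficients respond to.** Write the model as y = Xβ + error, with a column of ones in X for the intercept. Add a constant c to every final score. The least-squares solution becomes β̂ + c·(1, 0, …, 0). The intercept rises by c, and every slope, residual and standard error is unchanged. No slope can therefore carry information about a uniform improvement.

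**3. What the intercept means.** Uncentred, it is the expected final score when every covariate is 0. With six items scored 1 to 5, the lowest initial score is 6 as a sum or 1 as a mean, so 0 cannot occur. Testing this intercept against zero is not testing change against zero.

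**4. What the frequency slope means.** With initial score in the model and both scores on one scale, this slope is the same as in a regression of change on frequency. It shows whether people who listened more changed more. It can be zero when everyone improves equally, and non-zero when the mean change is zero.

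**5. Illustration by simulation.** There were 4,000 runs per setting with n = 60 and SD of change 3.4. Assumed: correlation 0.5, baseline mean 20, both scores on one scale, and covariates (including age and education) unrelated to change. Rejection rates at 0.05:

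| Test | No change | Change of 1.24 |
|---|---|---|
| Slope on initial score | 98.1% | 97.8% |
| Slope on frequency | 4.9% | 5.5% |
| Slope on usability | 4.7% | 5.3% |
| Paired t-test | 5.3% | 79.3% |

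Only the paired test distinguishes the two situations. No rate is quoted for the intercept, because it depends heavily on which covariates are assumed.

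**6. Can the change be formed?** If items are summed, Part A runs from 6 to 30 and Part B from 12 to 60. A participant who answers 3 throughout scores 18 and then 36, an apparent gain of 18 with no change. Raw totals cannot be subtracted.

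**The case against.** Several points on the other side have force.

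- **The mean change is not out of reach.** Descriptive means before and after will be reported. On a common scale the fitted model also gives the mean change, as a₀ + (b − 1) × mean initial score + the sum of each other slope times its covariate mean. A reader might infer that the plan can never yield the change; that goes too far. The defect is that no such contrast is defined.
- **The plan does not say that a significant slope or intercept will be read as improvement.** A reader might infer a very high false-positive rate from the 98% in the table. The article does not support that, because it designates no decisive coefficient.
- **Use of the application is tested in one sense.** The Intervention section sets no minimum use, so frequency varies and its slope tests a dose-response association. That is relevant to the hypothesis, but it is not the mean change that the sample size assumes.
- **A regression of final on initial score needs no common scale, whereas a change score does.** This stands, and it makes the remedy conditional.
- **A separate analysis plan might add the test.** The article does not leave the matter open: it assigns the hypothesis to a named model and writes out the equation.

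**Conclusion.** The concern holds in this form: the protocol article gives its hypothesis to a model in which no coefficient equals the mean change, and the test behind the 60 participants is not in the analysis section. This rests on algebra and on the article's own text. The simulation only illustrates it, under an assumed correlation and assumed covariates.

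The sample-size figure is not wrong. It reproduces at 59.01, rounded up to 60, with exact power of about 0.79, if 3.4 is the SD of the difference and the test is two-sided.

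Whether the change can be computed depends on the scoring and item overlap of Parts A and B. The article refers to the S1 Appendix for details of the questionnaire, and that appendix is not shown.

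**What to change.** 1. **Primary analysis.** Name the mean paired change (final minus initial) with its 95% confidence interval and a paired t-test. The intercept of a change-score regression with baseline covariates centred at their sample means gives the same estimate. Its ordinary standard error, however, treats the covariates as fixed. Under the simulation's assumptions the residual variance is (1 + 0.5)/2 = 0.75 of the variance of change, and that test rejected in 9.5% of runs with no change. If the adjusted form is preferred, its standard error should allow for covariates being sampled; otherwise the paired t-test should stand.
2. **Score.** Compute the change on items common to Parts A and B, or on one common scale (for example the mean per item, if the items measure the same content). State the power in terms of that score: what carries over is the ratio 1.24/3.4 = 0.365, not the raw points.
3. **If there are no comparable items,** the change cannot be formed, and the power statement must be withdrawn.
4. **Regression.** Label the final-score model and the exploration of confounders and modifiers as exploratory analyses of correlates of the final score.

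The cost is rewording of the Statistical analysis section and a defined common score. No new participants are needed.

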### Intervention

The intervention will consist of the use of the audiobook application for 4 weeks. During this period, the application will record the following data autonomously:

older adult id,date, hour and time that the older adult listened to each poem,poems listened.

This data will be stored locally and sent to a server for remote storage when the older adult has internet access.

Considering the hypothesis, there is no minimum application frequency of use to be suggested to participants. Thus, older adults should use the audiobook application according to their time availability and their motivation. Furthermore, participants are advised to abstain from any other emotional, social and/or motor training during the intervention period.

After two weeks of application use, the researchers ([name], [name], [name]) will carry out a follow-up in order to answer any questions that may arise from the use of the application, and explain again the objectives of the research, if necessary. This follow-up will be initially done by telephone, and in person if required.

After four weeks, the older adult will be invited to a meeting at the CRC, on a schedule to be agreed beforehand, to answer the well-being questionnaire (Part B) and a validated Spanish usability questionnaire (SUS [33, 34]).

Finally, data analysis will be carried out once the data gathering is finished.

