### Outcome measures

The following variables will be recorded:

Socio-demographic and digital competences variables
Age: number of years since the older adult was born until the day of the interview.Gender: man or women according to own definition.Education level: number of years of formal schooling completed by the older adult.Digital competences: set of knowledge, skills, and attitudes required when using Information and Communication Technologies and digital media to perform tasks, solve problems, communicate and manage information, and build knowledge efficiently, appropriately, and autonomously. It will be measured through a questionnaire based on DIGCOMP [31]. In it, five areas of relevant competences are identified: information and data search, communication and collaboration, digital content creation, safety, and problem solving. The questionnaire allows to determine the older adults’ competences. The way to categorize the digital competences of each participant is described in the same work by García Díaz and Villafañe [31].Dependent variables. These variables are related to well-being perception, and will be measured through a questionnaire specifically created by the authors to know the well-being of the older adults before (Part A) and after (Part B) the use of the audiobook application. Part A includes 6 questions and Part B includes 12 questions that are assessed with a 5-point Likert subjective scale (1 strongly disagree and 5 strongly agree). These questionnaires measured the following types of well-being: Hedonic, Eudaimonic, and Social.Independent variables.
Usability: It is the ease with which users can use software. It will be measured through the System Usability Scale (SUS) questionnaire [34]. It consists of 10 questions that are assessed with a 5-point Likert subjective scale (1 strongly disagree and 5 strongly agree). The result is between 0 and 100; the higher the result, the higher the usability level of the application. The overall score calculation method is detailed in the work of Sevilla-Gonzalez et al. [34], and the results interpretation can be found in Bangor et al.’s research [35].Frequency of use of the application: Number of poems listened to per day.

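### The hypothesis regression controls for frequency of use and usability, both post-baseline, does not name baseline digital competence, and has no slope that tests mean pre-post change

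*Protocol article*

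**What the plan says.** All places are in the Protocol article.

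- **Role of the model.** Statistical analysis: "the study hypothesis will be carried out using a multivariate linear regression", with final well-being as the response, "controlled by the initial well-being, and by sociodemographic variables, usability and frequency of use". The displayed equation repeats the frequency, usability and gender terms and ends with an open term for further demographic confounders or effect modifiers.
- **Frequency of use.** Outcome measures: "Frequency of use of the application: Number of poems listened to per day". The app logs this during the four weeks. The Intervention section sets no minimum: "older adults should use the audiobook application according to their time availability and their motivation".
- **Usability.** After four weeks participants attend a meeting "to answer the well-being questionnaire (Part B) and a validated Spanish usability questionnaire" (Intervention). Data collection procedure also places it in the exit assessment: "In addition, the usability questionnaire (SUS) will be applied to the older adults to assess the audiobook application’s usability".
- **Digital competence.** Data collection procedure, at baseline: "we will apply the DIGCOMP questionnaire to assess the older adults". The same section limits sociodemographic data to age, gender and education and introduces digital competence as a separate step. Neither the model sentence nor the equation names it.
- **Design and sample size.** The Design section describes one group compared with itself before and after. The Recruitment section sizes the study to reject a zero pre-post difference.

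**The concern.** Both app-related covariates arise after the intervention has begun. Frequency of use is a choice, driven by spare time and motivation that are not recorded. Usability is a rating given alongside the outcome. It may be a consequence of use, and it may share the participant's mood that day.

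This creates three risks:

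- **Self-selection.** People who are more able or more motivated may both listen more and feel better.
- **Over-adjustment.** If use affects well-being partly through finding the app easy, holding usability fixed removes that part.
- **Same-session rating.** Two self-ratings from one visit can correlate for reasons unrelated to the app.

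Because there is no control arm, there is no treatment coefficient. A reader looking for evidence about the app will turn to the frequency and usability slopes. Those slopes do not answer the research question, which is whether well-being improves on average.

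**Working it through.** **1. What the sample size is for.** The Recruitment section gives a difference of 1.24, an SD of 3.4, power 0.80 and error probability 0.05. Taking the SD as that of the difference and the test as two-sided, with the normal approximation:

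n = (3.4 × (1.960 + 0.842) / 1.24)² = 59.01, rounded up to 60.

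The stated N reproduces. Power at 60 is 0.806 by the normal approximation and 0.794 by the paired t test. So N = 60 is for a test of mean change.

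**2. What the planned slopes test.** In a simulated data set of 60, a constant of 0, 1.24 or 5 was added to every final score, and that score was regressed on initial score, frequency and usability:

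| Added shift | Intercept | Initial | Frequency | Usability |
|---|---|---|---|---|
| 0 | 0.045 | 0.365 | 0.340 | −0.195 |
| 1.24 | 1.285 | 0.365 | 0.340 | −0.195 |
| 5 | 5.045 | 0.365 | 0.340 | −0.195 |

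Only the intercept moves. No slope carries information on mean change. With uncentred covariates the intercept does not isolate it either.

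**3. Self-selection at n = 60 (assumed paths).** A baseline trait correlates 0.5 with use, 0.5 with usability, and r with the final score after the initial score is removed. Use has no effect. Then use and usability correlate 0.5 × 0.5 = 0.25, and each correlates 0.5r with the residual outcome. The standardised frequency slope is:

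- initial score only: 0.5r, which is 0.15 for r = 0.3 and 0.25 for r = 0.5;
- with usability added: 0.5r × (1 − 0.25) / (1 − 0.25²) = 0.4r, which is 0.12 or 0.20.

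Simulated share of trials with a significant frequency slope at 5%:

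| Adjustment, besides initial score | r = 0.3 | r = 0.5 |
|---|---|---|
| Usability (as planned) | about 14% | about 33% |
| None | about 21% | about 49% |
| Usability and the trait, measured perfectly | about 5% | about 5% |
| Proxy for the trait, squared correlation 0.25, no usability | about 14% | about 33% |
| Proxy, squared correlation 0.50, no usability | about 10% | about 19% |

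With r = 0 the planned model rejects in about 5%; with r = 0.2, in about 9%.

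**4. Over-adjustment (assumed paths, large sample).** There are no shared causes. Use acts directly on well-being with 0.30, on usability with 0.3 or 0.5, and usability acts on well-being with 0.3. The total effect of use is 0.30 + 0.3 × 0.3 = 0.39, or 0.30 + 0.5 × 0.3 = 0.45. The model with usability returns 0.30 in both cases.

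**5. Same-session rating (assumed paths).** Exit-day mood acts on usability and outcome (0.3 to 0.5), use acts on usability (0.4), and use has no effect on outcome. The planned model gives a frequency slope of −0.04 to −0.12 and a significant usability slope in 12% to 55% of trials.

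**6. Unmeasured motivation (assumed paths, large sample).** Digital competence and motivation each act on use, usability and outcome with paths of 0.2 to 0.4, and use has no effect. The planned model returns a frequency slope of 0.035 to 0.197. Dropping usability and adding digital competence returns about 0.04 to 0.14. Only adjusting for motivation as well brings it to zero.

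**The case against.** The article describes the regression as characterising final well-being and nowhere claims a dose-response. As descriptions of association the slopes need not be biased, and there is no treatment coefficient to bias. This stands. A reader might infer that the coefficients are biased outright, but that needs a causal target and path strengths the document does not supply.

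A reader might also take the 14% and 33% as damage done by adjusting for usability. They are not: in that set-up usability partly stands in for the trait, and leaving it out raises the rates to about 21% and 49%. The figures show confounding of frequency by an unadjusted trait. Nor does the return to about 5% promise a cure, since it requires the trait to be perfectly measured and the only confounder.

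Saying that digital competence is left out would be too strong. Outcome measures lists it under a joint heading with the sociodemographic variables, the equation has an open term, and covariates will be explored as confounders or modifiers. The text permits its inclusion without committing to it.

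Usability is rated, not chosen; only frequency is self-selected. One might also suppose that multiple imputation would invent usability scores for people who never open the app. The document does not say that such people would leave the questionnaire blank, and everyone is shown the app at induction, so that is speculation.

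None of this answers the main point: the model assigned to the hypothesis contains two post-baseline terms and no slope that tests mean change.

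**Conclusion.** The point holds in a limited form. From the text alone, four things are certain: frequency and usability are both post-baseline and sit in the hypothesis model; use is self-selected; digital competence is measured at baseline but not named in the model; and no slope tests the change for which N = 60 was calculated.

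The frequency and usability slopes therefore cannot be read as effects of the app. How far they would mislead is not determined by the document. Under the assumed trait the false-positive rate for frequency runs from the nominal 5% with no trait-outcome link to about 14% or 33% at correlations of 0.3 or 0.5. The N = 60 calculation is unaffected.

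**What to change.** 1. Make the hypothesis analysis an estimate of mean pre-post change with a confidence interval. Use a paired analysis, or regress the change on mean-centred baseline covariates and report the intercept. The two give the same point estimate. The regression standard error treats the covariate means as fixed, so the paired interval is the safer one to report.
2. State how both scores are put on the same scale. Outcome measures gives Part A 6 questions and Part B 12, so raw totals are not directly comparable.
3. If covariates are used, restrict them to baseline: initial score, age, gender, education and digital competence, named explicitly.
4. Move frequency of use to a separate exploratory association model that adjusts for digital competence. State that confounding by unmeasured motivation and available time remains, and do not present the slope as a dose-response.
5. Report usability on its own as a descriptive outcome.

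The cost is analysis wording only, since every variable is already collected. The small downside is that the frequency and usability slopes no longer form part of the hypothesis analysis.

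### The regression that decides the hypothesis lets data-driven confounders and modifiers in, and none of its terms is tied to the zero pre-post difference on which the trial was sized

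*Protocol article*

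**What the plan says.** **Analysis.** The Statistical analysis section of the protocol article states: "Then, the study hypothesis will be carried out using a multivariate linear regression". The outcome is the final well-being score. The displayed equation has an intercept and slopes for initial well-being, frequency of use, usability and gender. Its last term is defined as "Slopes associated with other confounding demographic variables or relevant modifying effects". How those further terms are found is also stated: "We will explore if the covariates play a role of confounding effects and/or modifiers in the relationship between the initial and the final well-being score". No coefficient is singled out as the one that decides the hypothesis.

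**Sizing.** The Recruitment section plans the trial by "considering a pre-post difference of 1,24 points on the mental health outcome" and "a potential standard deviation of 3,4". The aim is to "reject the null hypothesis that the response difference is zero with power 0,8 and an error probability of 0,05". That is one null hypothesis about one mean change.

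**Candidates.** Data collection procedure lists the demographics as age, gender and educational level. Outcome measures groups digital competences with them.

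**The concern.** There are two faults, and both lie in what the text states.

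First, exploration and confirmation share one model. Looking for confounders and modifiers is harmless in a separate, labelled analysis. Here the result of the search becomes a term in the equation that carries the hypothesis. Terms would be kept because they look relevant in these 60 people, and the model's p-values and intervals would then be read as if its form had been fixed beforehand.

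Second, the null used for sizing does not reappear in the analysis. A reader of the results could not say which estimate confirms or refutes the hypothesis of a positive change, so the stated 0.05 is attached to no particular test.

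**Working it through.** **1. The planned size reproduces.** Inputs from Recruitment: difference δ = 1.24, SD = 3.4 (taken as the SD of the paired difference), power 0.80, error 0.05.

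n = [(z₀.₉₇₅ + z₀.₈₀) × SD/δ]² = [(1.960 + 0.842) × 3.4/1.24]² = 59.0, rounded up to 60.

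One-sided 0.05 would give [(1.645 + 0.842) × 3.4/1.24]² = 46.5, that is 47. The planned 60 therefore matches a two-sided 0.05 test of mean change, although the text does not state the sidedness.

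**2. The regression slopes do not test that null.** Write the model as final = a₀ + b₁·initial + b₂·frequency + b₃·usability + b₄·gender + further terms. Add a constant c, for example 1.24, to every participant's final score. The least-squares fit returns a₀ + c and exactly the same slopes. A uniform improvement is thus invisible to every slope. The intercept as written does not serve either: it is the expected final score when initial well-being and all other covariates are 0, which is not the mean change.

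**3. Cost of the open search for one named slope.** Simulation at n = 60 with no true covariate or modifier effect. Assumptions, not in the documents: initial-final correlation 0.5; correlation among covariates 0, 0.3 or 0.5; the analyst keeps the covariate set that gives the frequency slope its smallest p-value.

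| Rate of p < 0.05 for the frequency slope | corr. 0 | corr. 0.3 | corr. 0.5 |
|---|---|---|---|
| Fixed model (4,000 runs) | 4.5% | 4.9% | 4.7% |
| Age, gender and education all optional (4,000 runs) | 6.4% | 7.9% | 8.8% |
| Gender kept, as in the equation; age and education optional (6,000 runs) | 5.7% | 6.8% | 7.6% |

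With five independent optional covariates (32 subsets, 3,000 runs) the rate is 7.8%.

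**4. Cost of not naming the slope.** If either frequency or usability could count as support, the rate for independent tests is 1 − 0.95² = 9.75%. Simulation with a fixed model and independent covariates (10,000 runs) gives 10.1%. Counting only positive slopes gives 5.35%, about twice the 2.5% that a single named slope would have in that direction.

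**5. After repair.** One pre-named coefficient in a fixed model returns the nominal level (5.35% in the same 10,000 runs, Monte Carlo standard error about 0.2 percentage points).

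**The case against.** **Most main effects are already stated.** This is right. Four terms are fixed, and the text names sociodemographic control. Only the retention of the other demographics and the entry of modifiers are open, so the model as a whole is not found by searching.

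**The search is called exploratory, and it concerns the initial-final relation rather than the effect of the app.** Both parts are true of the sentence. The definition of the last term nevertheless puts the result into the hypothesis model.

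**A named coefficient, a retention rule and centring normally belong in an analysis plan.** This is also fair, and their absence alone would be no finding. What remains is stated text: a search inside the deciding model, and a sizing null that the model's slopes cannot test. A later plan could settle both only by departing from what the protocol says.

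**A stronger reading is tempting.** With five non-baseline slopes (frequency, usability, gender, age, education), the chance of at least one p < 0.05 is 1 − 0.95⁵ = 22.6%, or about 21-22% simulated. Adding five interactions with initial well-being gives 1 − 0.95¹⁰ = 40.1%, or 36-39% simulated. A reader might infer a roughly sevenfold error rate. The documents do not support that. The figures hold only if any covariate slope or interaction were taken as support. The protocol treats these terms as control variables, and nowhere says that a gender, age or education slope would confirm its hypothesis.

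**Conclusion.** The concern holds at modest size. The hypothesis model admits terms chosen from the same data, and none of its terms is tied to the null on which the trial was sized. The missing link to a deciding contrast is the more basic fault; the covariate search is the lesser one.

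For one named slope, the search takes the error from about 5% to about 6-9%, and to about 6-8% if gender stays in as the equation has it. Leaving open whether frequency or usability decides gives about 10%. These figures rest on the assumed correlations, and the search figures also on a smallest-p rule that the protocol does not state, so they are upper bounds for a search of that kind.

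**What to change.** 1. Name the mean pre-post change in well-being as the single deciding contrast, tested at two-sided 0.05, the level that reproduces 60. Parts A and B must first be scored comparably, since Part A has 6 questions and Part B has 12.
2. Obtain it, for example, as the intercept α in: final − initial = α + β₁(initial − mean) + β₂(age − mean) + β₃(gender − mean) + β₄(years of education − mean) + error. With mean-centred covariates, α is the mean change, and the test is α = 0.
3. Fix those four baseline covariates in advance and keep them whatever their significance, with no data-driven addition or removal.
4. Remove the modifying-effects part of the last term from the hypothesis model. Fit modifier terms only in separate models labelled exploratory, and report estimates with 95% intervals and no confirmatory claim.
5. Report the frequency and usability slopes as descriptive associations. Both are measured during or after the intervention.

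**Cost.** A few sentences in the analysis section, with no new data or participants. Modifier and single-slope results can no longer be presented as confirming the hypothesis. The four covariates use a few degrees of freedom: 60 − 5 = 55 residual, against 59 for the unadjusted paired test.
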